### Patient inclusion and exclusion criteria

Inclusion criteria are an age of 18 years and older, a score on the Dutch version of the EK-10 of 20 or higher, and/or at least one yes on the added questions 11 through 16. Exclusion criteria are an age under 18 years, suicidal ideations, dementia or other severe cognitive disorders, psychotic disorder, bipolar disorder, dependence on alcohol or drugs, unstable severe medical condition as diagnosed by their GP, insufficient knowledge of the Dutch language to fill out the questionnaires, or having received psychological treatment in the six months before the start of the study or recognised with anxiety or depressive symptoms by their GPs in this period.

### Sample size

The primary outcome measure for the evaluation of the effectiveness of tailored interventions is the recognition of anxiety or depressive disorders by GPs in patients with symptoms that might indicate these conditions. The rate of recognition was reported at about 45% [14,36]. Studies showed that interventions focused on professionals' adherence to guidelines can increase adherence by 10% [27]. With tailored interventions, we suppose the recognition can improve by 15%. To get an accurate estimate (alpha = 0.05; power = 0.80) of a 15% difference (45% vs. 60%) in recognition between both groups, assuming that 5% of participants will drop out (loss to follow-up will be minimal because we will perform a retrospective medical record search to get insight in rate of recognition) and considering an intracluster correlation of 0.01 [37], 396 patients in 22 practices have to be included.

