### Study design

A cluster RCT with two arms has been chosen for this study. Cluster randomisation was applied at the level of the general practice organisation. The general practice organisations were allocated to the intervention or the control group. The allocation was generated by an independent statistician.

The chosen implementation strategies are

1. an educational intervention targeted at GPs, comprising of one day of training at the start and one feedback at six months (in both study arms);

2. one or more interventions tailored to prospectively identified barriers in the local context of GPs (only in the intervention arm).

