### Recruitment of general practitioners

We aimed at recruiting patients and GPs in 22 general practices into our trial. Therefore, we prepared a newsletter for GPs with information about the goals of the study; the activities; and the accreditation they would receive if they followed the one-day training in guideline recommendations for the early recognition, diagnosis, and stepped-care treatment allocation of patients with anxiety or depressive disorders. Several recruitment strategies were carried out: (a) the newsletter was published at the website of the Dutch GPs association and the website of the Trimbos Institute, a centre of expertise on mental health and addiction and (b) the newsletter was sent to a sample of 500 GPs, provided by the Netherlands Institute for Health Services Research (NIVEL) and to all GPs who had a contract with a specific health insurance company that gives financial support. Subsequently, a researcher contacted all practices by phone to recommend participation. Finally, 23 general practices were included.

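### The planned 396 patients do not cover both stated allowances: with 5% drop-out and an ICC of 0.01, power is about 77-78%, not 80%

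*Protocol article*

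**What the plan says.** The Sample size section of the protocol article gives the whole calculation in one sentence.

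- The target is set as "To get an accurate estimate (alpha = 0.05; power = 0.80) of a 15% difference (45% vs. 60%) in recognition between both groups".
- The loss allowance is stated as "assuming that 5% of participants will drop out". A remark in brackets says that loss should be minimal because recognition is read from the medical records in retrospect.
- The clustering allowance and the result follow: "considering an intracluster correlation of 0.01 [37], 396 patients in 22 practices have to be included".

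The Study design section fixes the cluster: "Cluster randomisation was applied at the level of the general practice organisation". The Primary outcome section takes all patients included in the study as the denominator, and the Statistical analyses section plans a multilevel model on an intention-to-treat basis.

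**The concern.** Every input needed to check the 396 is printed, and the sentence reads as if drop-out and clustering were both already inside it. If so, taking both out again should return the sample size for an individually randomised trial. It does not: 396 × 0.95 / 1.161 = 324 patients, or 162 per arm, whereas the stated difference, alpha and power need 170 to 173 per arm.

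This is the power statement for the primary outcome. If the trial finds no difference, readers will weigh that result against a claimed 80% which the plan's own inputs do not quite give.

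**Working it through.** **Inputs from the Sample size section:** alpha 0.05; power 0.80; 45% and 60%; 5% drop-out; ICC 0.01; 396 patients in 22 practices, so 396 / 22 = 18 per practice.

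**Assumptions, not stated in the article:** two-sided test, 1:1 allocation (11 practices per arm), practices of equal size.

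**1. Unclustered requirement per arm**, with z values 1.960 and 0.8416.

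- Unpooled variance: (1.960 + 0.8416)² × (0.45 × 0.55 + 0.60 × 0.40) / 0.15² = 7.849 × 0.4875 / 0.0225 = 170.1, or 340.1 in total.
- Pooled variance under the null (Fleiss formula): [1.960 × √(2 × 0.525 × 0.475) + 0.8416 × √0.4875]² / 0.15² = 172.8, or 345.6 in total.

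**2. Reproducing the plan's figure: clustering only.** Design effect = 1 + (18 − 1) × 0.01 = 1.17.

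- Unpooled: 340.1 × 1.17 = 397.9.
- Fleiss: 345.6 × 1.17 = 404.4.

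The unpooled figure is 397.9 / 22 = 18.1 per practice; 18 per practice is 396. Power with all 396 analysed (effective n per arm = 198 / 1.17 = 169.2) is 79.8% unpooled and 79.2% by Fleiss. So 396 is reproduced, to within about 2%, with no allowance for loss.

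**3. Clustering and 5% loss together.** After loss the practice size is 17.1 and the design effect 1 + 16.1 × 0.01 = 1.161. Both versions are shown.

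| Formula | Design effect 1.161, / 0.95 | Design effect 1.17, / 0.95 |
|---|---|---|
| Unpooled | 415.7 | 418.9 |
| Fleiss | 422.4 | 425.6 |

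The requirement is about 416 to 426, which is 5.0% to 7.5% above 396 (415.7 / 396 = 1.050; 425.6 / 396 = 1.075). Fixing 22 practices and solving for the practice size gives much the same: 419 unpooled, 427 by Fleiss.

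**4. Power at 396 enrolled with 5% lost.** Analysed: 396 × 0.95 = 376.2. Effective n per arm: 376.2 / (2 × 1.161) = 162.0.

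- Unpooled: standard error √(0.4875 / 162.0) = 0.0549; 0.15 / 0.0549 − 1.960 = 0.77; power 78.1%.
- Fleiss: power 77.4%.

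**5. Other routes to 396.**

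- A one-sided alpha needs only about 318 to 330 patients.
- A continuity correction needs about 455 to 467.
- Loss without clustering needs 345.6 / 0.95 = 364.
- A cluster size near 9 gives 346 × 1.08 / 0.95 = 393, which is close. However, the practice is the randomised unit, and no such cluster size is stated.

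**6. Supplementary only.** Replacing the normal reference by a noncentral t with 20 degrees of freedom (22 practices less two arms), with the unpooled standard error, gives about 74% with the 5% loss and about 76% without it.

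**The case against.** The best defence is that the 5% may never reach the primary analysis. The outcome is read from medical records, the article itself expects minimal loss, and the denominator is everyone included. A patient who stops returning questionnaires can still be counted. If all 396 are analysed, power is 79-80% and the plan is essentially as stated. This stands as a reason to call the practical effect small. It does not make the printed sentence correct, because that sentence says that a 5% loss was allowed for.

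A second defence is that recruitment did better than planned: "Finally, 23 general practices were included". At 18 patients in each of 23 practices (414 enrolled, 393 after loss) power is back to about 79-80%. But the article does not say that the patient target was raised, and 396 patients spread over 23 practices still give only about 78%.

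Three stronger readings are tempting and are not supported:

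- **That the trial really has 74% power.** This rests on a small-cluster t reference that the article does not claim to have used. It is a separate convention, not an arithmetic error, and the choice of degrees of freedom for the multilevel test is commonly left to the analysis plan.
- **That failing to recalculate for 23 practices is a mistake.** The section gives the planned requirement; including one practice more does not oblige anyone to redo it.
- **That the ICC is too low and power far worse.** The 0.01 rests on a cited source that is not at hand, and nothing in the article supports a particular higher value. Barriers that differ between GPs do not fix how much recognition varies between practices.

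**Conclusion.** The point holds in a narrow form. The stated inputs, with both allowances applied, require about 416 to 426 patients, not 396. With 396 enrolled and 5% lost, power is about 77-78%, a shortfall of 2 to 3 percentage points. The most likely explanation is that the loss was left out of the calculation, since 396 fits the clustered size without it; the article does not show the steps, so this remains an inference.

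The result assumes a two-sided test, equal allocation and equal practice sizes. The choice between the two formulas moves the figures slightly but does not change the conclusion. This is an error in a stated figure, cheap to correct, and no threat to the design.

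**What to change.** Correct the sentence in the Sample size section in one of two ways, according to whether the loss applies to the record-based outcome:

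- If up to 5% of included patients may lack the primary outcome, keep the allowance and state that 396 enrolled (376 analysed) in 22 practices give about 77-78% power.
- If the records yield the outcome for every included patient, remove the 5% allowance and state about 79-80% power for 396.

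Either version should say that the test is two-sided and allocation 1:1, if that is what was meant. The cost is a sentence and, under the first option, a slightly less favourable power. No extra patients and no change to design or conduct are needed.

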### Intervention group

#### Tailored strategies

GPs from the general practices randomised to the intervention group will receive interventions that are tailored to prospectively identified barriers in their local context over the course of one year. Methods for tailoring implementation interventions to local barriers vary widely and are often poorly documented [31]. To get insight in the experienced barriers in the early recognition, appropriate diagnosis, stepped-care treatment allocation, and providing of information on the diagnosis and stepped-care treatment options for anxiety and depressive disorders, a semistructured face-to-face interview was carried out with each of the participating GPs by a trained interviewer. For this interview, we developed a checklist based on the main types of barriers to adherence to evidence-based guidelines on anxiety and depressive disorders by GPs [25,28,38]. Based on these main types of barriers, we developed interventions that could solve the barriers. Each interview was documented in a report. Based on this report, experts suggest interventions that may resolve the barriers. These interventions are fed back by telephone to the GP by the same interviewer.

The interviewer calls the GP once every two months to map the implementation process and links this back to the experts. Again, experts suggest interventions or give advice to the interviewer for the next contact with the GP. With a continuous feedback loop between the experts, the interviewer, and the GP, we optimise the tailoring process. All contacts between the experts, the GP visitor, and the GP are reported.

#### Training

GPs in both conditions received one day of training by experts in (a) the early recognition of high-risk patients with the Four-Dimensional Symptom Questionnaire (4DSQ), (b) appropriate diagnosis, (c) stepped-care treatment allocation, and (d) the providing of information to patients with anxiety and depressive disorders. The 4DSQ is a self-rating questionnaire measuring four dimensions of common psychopathology: distress, depression, anxiety, and somatization. The 4DSQ was developed in general practice. The principal aim of the 4DSQ is to distinguish between stress-related syndromes (denoted as 'stress', 'burnout', 'nervous breakdown') and psychiatric disorders (*i.e*., depression and anxiety disorders) [39]. The 4DSQ can be used in recognising high-risk patients for anxiety or depressive disorders and is recommended by the multidisciplinary guidelines on anxiety and depressive disorders. Criteria for high-risk patients are described in the clinical guidelines for anxiety and depressive disorders for general practice. In a former quality-improvement project, GPs showed positive experiences with the use of the 4DSQ in detecting anxiety disorders. The 4DSQ offers GPs a means to start talking with patients with unexplained somatic symptoms about possible psychological or psychiatric disorders.

Adequate diagnosis is based on the recommendations of clinical guidelines for general practice. Stepped-care treatment allocation is based on the multidisciplinary guidelines. According to the stepped-care model, patients with a noncomplex anxiety disorder or a nonsevere depressive disorder have to receive as a first step brief interventions, such as guided self-help or brief therapy. Patients with a complex anxiety disorder or a severe depressive disorder have to receive effective psychotherapeutic interventions, an antidepressant, or a combination of both. Determination of the complexity of an anxiety disorder is based on at least one of the following criteria: serious social/functional dysfunction, comorbidity (patient has another anxiety disorder or depression), obsessive compulsive disorder or posttraumatic stress disorder, no response after a minimum of six weeks and maximum 18 weeks, or no remission after a first-step brief intervention. Determination of the severity of a depressive disorder is based on at least one of the following criteria: high level of distress, serious social/functional dysfunction, minimum eight symptoms of the depressive disorder according to the fourth edition of the *Diagnostic and Statistical Manual of Mental Disorders *(DSM-IV) [40], psychotic features, suicidal ideation.

#### Feedback

GPs in both conditions were asked to fill out a consultation registration form for each patient who completed the 4DSQ. On this form, GPs need to register the score on the 4DSQ, the diagnosis, the indicated treatment, and if they informed the patient about the diagnosis and stepped-care treatment options. GPs received individual feedback on the number of registered 4DSQs, appropriate diagnosis, stepped-care treatment allocation, and information on the diagnosis and stepped-care treatment options in a report after six months, based on the consultation registration forms.

#### Control group

GPs from the general practices randomised to the control group only received training and feedback (see intervention group).

### Outcome measures

#### Primary outcome

The primary outcome for both conditions is the proportion of patients who have been appropriately recognised to have anxiety and/or depressive disorder. This proportion is calculated by dividing the amount of patients recognised by the GP by the total amount of patients included in the study. Recognition is measured by the registration of (a) anxiety or depressive complaints; (b) psychological complaints (anxiety, worrying, sorrow/grief, stress, feeling down and sleeping disorder, unexplainable somatic complaints); (c) the International Classification of Primary Care-1 (ICPC-1) codes [41] for anxiety and/or depression and/or related psychological problems, the same ICPC codes that were used in previous work by Smolders [17]; and (d) the 4DSQ score.

### Secondary outcomes

#### In patients

The secondary outcome measures in patients are severity of anxiety and depressive symptoms measured with the 4DSQ; level of functioning, measured with the World Health Organization's Disability Assessment Scale II [42]; expectation towards and experience with care, measured with the QUality Of care Through the Eyes of the patient (QUOTE) [43]; care utilisation, illness, and work, measured with the Trimbos/institute Medical Technology Assessment questionnaire for Costs associated with Psychiatric Illness (TiC-P) [44]; and quality of life, measured with the EuroQol (EQ-5D) [45]. Measurement will take place every three months: at baseline (T0) and at three (T1) and six months (T2) after inclusion.

#### In general practice

The secondary outcome measures for both conditions are proportion of patients for whom tricyclic antidepressants (TCA's) or selective serotonin reuptake inhibitors were prescribed and number of referrals to specialised mental healthcare. We gather data to calculate the secondary outcomes by performing a retrospective patient medical record search, after the last patient's follow-up measure.

#### Process evaluation

In a process evaluation, we describe the identification of barriers to change and the relationships between prospectively identified barriers and improvement interventions selected for use in the intervention group. We evaluate the experiences of GPs in the intervention group, the GP visitors and the experts with the tailoring process, the implemented changes in practice, and the factors influencing the tailoring process. To measure the experiences, semistructured interviews are conducted, and reports of the interviews are made.

To get an insight into the factors that influence the provision of guideline-recommended care in both groups, all GPs are asked to fill out an individual self-administered questionnaire about the general practice and GP characteristics. The practice characteristics include practice type, number of GPs in the practice, collaboration with other healthcare professionals working in the practice, and size of practice population. The GP characteristics include demographic data, interest and attitudes towards depressive and anxiety disorders, and questions to assess barriers to healthcare provision to patients with depressive or anxiety disorders and, for implementation of the depression and anxiety guidelines, collaboration with professionals and institutions specialised in mental healthcare and GPs' levels of burnout. This questionnaire is developed and used in the Netherlands Study of Depression and Anxiety, an eight-year longitudinal cohort study designed to be representative of persons with depressive and anxiety disorders in different healthcare settings and in different stages of the disorders [24,46]. The questionnaire is filled out twice: before the start of the tailoring process and when the tailoring process is finished.

#### Economic evaluation

An economic evaluation will be conducted to estimate the cost effectiveness of the tailored intervention from a societal perspective. The between-group difference in costs will be related to the difference in benefits in terms of health-related utilities. This economic evaluation uses the EQ-5D. The cost-utility analysis measures health in quality-adjusted life years (QALYs), derived using the EQ-5D questionnaire [47]. The EQ-5D characterises five health dimensions (mobility, self-care, usual activities, pain, and anxiety/depression), each rated using three levels (no problems, moderate, and severe problems). Responses will be transformed into a health utility score that ranges between 0 = dead and 1 = full health. Health utilities will then be used to calculate the QALYs. This gives a comparison of how many QALYs individuals in each group gained on average as a result of the tailored intervention. Results can statistically be compared to see if there are any differences. The final step of the cost-utility analysis will be to compare the cost of the QALY gains in each group.

The costs of the implementation strategy used will be studied for each practice. These costs are (a) the costs per hour of the GP visitor and experts for the activities during the tailoring process and the one-day training and feedback, (b) material costs for the one-day training, and (c) the costs per hour of the GP related to the implemented interventions. In addition, the difference in healthcare costs related to the diagnostic process will be included, including number of consultations, diagnostic tests, and referrals with diagnostic aims. Healthcare costs will be measured by the TiC-P. The costs will be estimated in line with the Dutch guidelines for cost calculations in healthcare [48].

Apart from costs of the tailored strategy, healthcare costs, and costs of production losses, indirect costs will be measured for both groups related to the severity of anxiety and depressive symptoms, level of functioning, experience with care, and quality of life.

### Statistical analyses

The adequacy of randomisation is assessed comparing characteristics of the general practice and GPs that might influence the outcomes (see process evaluation). Recognition of anxiety or depressive disorders in eligible patients in the study period is compared between the intervention and control groups, taking into account clustering of data in a multilevel regression model. We will also calculate and compare the percentages of patients who have been appropriately recognised and diagnosed, prescribed antidepressants, and referred and the number of consultations, determined by the registration in patients' medical records.

Descriptive statistics will be used to outline the characteristics of practices and GPs. Finally, bivariate and multivariate multilevel regression analyses will be performed to identify factors associated with better adherence to specific guideline recommendations. All analyses will be performed on an intention-to-treat basis. Possible confounding characteristics (*e.g*., age, gender) will be included in the statistical models.

In addition, we will describe the barriers for change that were identified and the relationships between prospectively identified barriers and improvement interventions selected for use, based on an analysis of the records from the contacts between the GP and the interviewer. Data about the experiences of participants in the tailoring process, the implemented changes in practice, and their ideas about influencing factors will be structured, interpreted, and described in a qualitative way.

Direct and indirect costs of the interventions will be reported. The results of the cost will be presented as mean values with standard errors. Cost effectiveness will be presented in incremental cost-effectiveness ratios. The uncertainty will be assessed using bootstrapping, and acceptability curves will be presented [49]. A principled method for dealing with missing data will be applied to the economic evaluation [50].

### Ethical principles

The study protocol has been approved by the Medical Ethical Committee of the Institutions for Mental Health (METiGG; Utrecht, the Netherlands) in 2009.

## Discussion

Early recognition, diagnosis, and stepped-care treatment allocation in patients with anxiety or depressive disorders in general practice is dependent on a variety of factors influencing GP performance. The study gives information about the relevant barriers for improvement and whether they differ between GPs. Designing implementation interventions that are tailored to prospectively identified barriers for improvement in the local context of GPs could lead to more guideline-recommended care. Different studies have investigated the impact of tailored interventions for behaviour change in GPs, to improve the quality of care, in an RCT, but little is known about what methods and models of tailoring are effective and efficient [31,32]. The aim of this RCT is to determine the effectiveness of tailored interventions to improve the implementation of guideline recommendations for the early recognition, diagnosis, and stepped-care treatment allocation for anxiety and depressive disorders in primary care and describe the methods used in the process of tailoring. Because the performance of GPs during the tailoring process may be influenced by policy developments, personal attention, or even external financial incentives, the relationships between prospectively identified barriers and improvement interventions selected for use will be described, as well as the factors that influence the provision of guideline-recommended care.
